## 1 PURPOSE OF THE STATISTICAL ANALYSIS PLAN

This document describes the statistical methodology that will be used to meet the objectives of the study as well as all the analyzes that will be performed and methods of deriving variables.

The analysis of the impact of the intervention on the overall cost of patient care (secondary objective) will be carried out separately by a medico-economic service and will not be described in this SAP.

The analysis of the impact of the intervention on the quantity and type of drug prescriptions (secondary objective) will be the subject of a thesis by a pharmacy student and will therefore not be described in this SAP.

The statistical analysis will begin after the validation of this analysis plan by the scientific council of the study and reception of the cleaned and frozen database.

## 2 CHANGES IN RELATION TO THE PROTOCOL

Contrary to what is stated in the protocol, the statistical analyzes will not be performed blind. This is not possible given the differences between the data collected in the 2 groups (i.e. geriatric assessment and multidisciplinary team meetings (MDTM) performed only in the intervention group).

## 3 SUMMARY OF THE PROTOCOL

### 3.1 Main Objective

The objective of our project is to evaluate the impact of a systematic detection of dementia cases carried out with residents of Nursing Homes (NH) during a MDTM on the use of the care system and more specifically on the admission rate to emergency department (ED).

Like MDTM in oncology, this MDTM on Alzheimer's disease and related diseases aims to discuss the diagnosis of dementia and the health project of NH residents according to a simplified Comprehensive Geriatric Assessment (CGA) carried out by the coordinating physician.

|                    |                                                                   |                                                                                                            |
|--------------------|-------------------------------------------------------------------|------------------------------------------------------------------------------------------------------------|
| Principal analysis | Statistical Analysis Plan (SAP)-IDEM Study 0910701
Version 1.0 | [figure not shown]
Hôpitaux de Toulouse |
|                    |                                                                   | 07/22/2016                                                                                                 |

### 3.2 Secondary Objectives

The secondary objectives of this study are to determine the impact of systematic detection of dementia during MDTM on:

- the quantity and type of drug prescriptions (neuroleptics, benzodiazepines, antidepressants, hypnotics, anxiolytics, thymo-regulators, anti-cholinesterases, memantine) and non-drug treatments (physiotherapy, occupational therapy, psychological counseling, dietetics, speech therapy),
- the appropriateness or inappropriateness of hospitalizations (including emergencies),
- the prevalence of psycho-behavioral disorders,
- the residents' process of entry into the dependency,
- the residents' quality of life,
- the burden of the NH staff
- the advanced care planning measures (advance directives ...)
- and the overall cost of care.

### 3.3 Calculation of the number of subjects

The number of subjects required to meet our main objective was calculated by assuming a bilateral test with an alpha risk of 5% and a beta risk of 20% (80% power). On the basis of REHPA survey data (Rolland Y et al. 2009), 13.5% of all residents reported in the REHPA survey were admitted to hospital services in 3 months, an estimate of 54% in 1 year. By limiting the population of the REHPA survey to subjects with the inclusion criteria defined in IDEM, 12% were admitted to hospital services in 3 months, an estimate of 48% at 1 year. According to the same survey, of the 48% of all hospitalizations, half were via ED. Indeed, we can estimate an incidence of ED transfers of 24% at 1 year in the non-intervention group. Assuming a 30% reduction in the ED transfer rate in the intervention group, the 12-month ED transfer rate will be 16.8%. 516 subjects are needed in groups, taking into account the cluster effect with an ICC set at 0.02 of an attrition rate of 20% (average known % of deaths per year from REHPA data), the minimum number of subjects per group varies from 950 to 1050 depending on the inflation factor linked to the contamination between the groups, which has been varied from 5 to 10%.

|                    |                                                                   |                                                                                                            |
|--------------------|-------------------------------------------------------------------|------------------------------------------------------------------------------------------------------------|
| Principal analysis | Statistical Analysis Plan (SAP)-IDEM Study 0910701
Version 1.0 | [figure not shown]
Hôpitaux de Toulouse |
|                    |                                                                   | 07/22/2016                                                                                                 |

In total, 1,000 residents per group or 2,000 residents must be included. Taking into account an inclusion number of 30 residents on average per NH, 35 institutions per arm are necessary. Given the potential of 240 NH of REHPA network, this number of institution is realistic to achieve. In total 89 nursing homes have volunteered.

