## 4 EVALUATION CRITERIA

### 4.1 Primary endpoint

The primary endpoint of this study, collected by subject, will be the occurrence of at least one admission to a hospital ED during a one-year follow-up period (i.e., yes / no binary criterion).

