Population of analysis: The main analysis of the primary efficacy endpoint of the intervention will be carried out on the subjects of the ITT population. Thus, subjects who left the study before 1 year of follow-up will still be considered in this analysis if their follow-up is at least 1 month. For example, a patient who died after 4 months of follow-up without ED transfer will have a primary endpoint equal to "No". This will lead to a possible underestimation of the rates of subjects admitted to ED in 1 year in the 2 groups but should not bias the comparison between the groups since the follow-up times should be close between the 2 groups.

As sensitivity analyzes, this analysis will also be performed on the PP1 population in addition to the ITT analysis.

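### The 24% planning rate is four times a quarterly proportion, halved, which does not fit an at-least-one endpoint (about 22% does); the attrition allowance for deaths is mismatched too, and the two errors largely offset in power

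*SAP*

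**What the plan says.** SAP section 3.3 starts from survey data on residents admitted over three months. For all residents, 13.5% "were admitted to hospital services in 3 months, an estimate of 54% in 1 year". For residents meeting the trial's criteria, "12% were admitted to hospital services in 3 months, an estimate of 48% at 1 year". Both annual figures are the quarterly figure times four. The SAP then states that "of the 48% of all hospitalizations, half were via ED" and concludes that "we can estimate an incidence of ED transfers of 24% at 1 year in the non-intervention group". A 30% relative reduction gives 16.8% in the intervention group, and 516 per group before inflation. An ICC of 0.02, 20% attrition (described as the yearly share of deaths) and 5–10% for contamination raise this to 950–1,050, set at 1,000. The summary at the front of the SAP repeats the 24%, the 20% and the 1,000.

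Section 4.1 defines the primary endpoint per resident as "the occurrence of at least one admission to a hospital ED during a one-year follow-up period". Section 6.1 keeps anyone with at least one month of follow-up: "a patient who died after 4 months of follow-up without ED transfer will have a primary endpoint equal to" No. The same paragraph accepts that the rates may be underestimated as a result.

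**The concern.** The 12% is a share of residents. Adding four quarterly shares counts a resident admitted in two quarters twice. The sum equals the share with at least one admission in the year only if nobody is admitted in more than one quarter. The SAP neither states nor defends that condition, and it varies only the contamination factor, never the control rate. The 24%, the 16.8%, the 516 and the 80% power all rest on this step.

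There is a second mismatch. The sample size removes the residents who die, while the primary analysis keeps most of them as No. The planning calculation therefore matches neither the endpoint nor the analysis population. What is at stake is how the result is read. A null finding would be judged against a stated 80% power for a 30% reduction, and an observed control rate near 20% could be taken for unexpectedly low risk when the plan's own inputs point to it.

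**Working it through.** **1. The SAP's figure.** Inputs from section 3.3: 24% vs 16.8%, two-sided 5%, 80% power. Unpooled formula: n = (1.96 + 0.8416)² × [0.24×0.76 + 0.168×0.832] / 0.072² = 7.849 × 0.3222 / 0.005184 = 487.8. Continuity correction: (n/4) × [1 + √(1 + 4/(n×0.072))]² = 515.2, rounded up to 516. The figure reproduces, so everything after the 24% is sound.

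**2. The annual rate.** Half of 12% is 6% per quarter via the ED. With equal, independent quarters, 1 − 0.94⁴ = 21.9%. A 30% reduction gives 15.3%.

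**3. Effect of this step alone.** Same formula: 7.849 × (0.1712 + 0.1299) / 0.0658² = 546.3 (with unrounded rates), and 576.3 after correction, so 577 per group; 577/516 = 1.12. A design with exactly 80% power at 24% then has Φ(2.8016 × √(515.2/576.3) − 1.96) = Φ(0.689) = 75%.

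**4. Deaths kept as No.** Take constant hazards of −4 ln 0.94 = 0.2475 (first ED admission) and −ln 0.80 = 0.2231 (death), total 0.4706. The share with an ED admission before death within one year is (0.2475/0.4706) × (1 − e^(−0.4706)) = 0.526 × 0.375 = 19.7%. A 30% reduction gives 13.8%. Deaths in the first month do leave the analysis population, but that is only 1 − 0.8^(1/12) = 1.8% and is ignored here.

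**5. Power for 1,000 per group.** Effective n = 1,000 × (share retained) / contamination factor / [1 + (m − 1) × 0.02], where m is the number of residents per nursing home (NH). Section 3.3 gives m = 30 on average. The value 24 is 30 less 20%. The SAP does not say which m entered its design effect: 516 × design effect / 0.8 × 1.05 to 1.10 gives 989–1,036 with m = 24 and 1,070–1,121 with m = 30. Power = Φ(difference / √(variance sum / effective n) − 1.96), unpooled, without continuity correction, for contamination 10% to 5%:

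| Inputs | Effective n, m = 30 | Power, m = 30 | Effective n, m = 24 | Power, m = 24 |
|---|---|---|---|---|
| SAP: 24%, 20% lost | 460–482 | 77.7–79.5% | 498–522 | 80.8–82.6% |
| Rate corrected only: 21.9%, 20% lost | 460–482 | 73.0–74.9% | 498–522 | 76.3–78.2% |
| Both corrected: 19.7%, deaths kept | 575–603 | 76.9–78.8% | 623–652 | 80.1–81.9% |

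At equal m, the first and third rows differ by less than 1 point. Solving the power expression for 80% in the third row gives a detectable reduction of 30.4–31.1% at m = 30 and 29.3–30.0% at m = 24.

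**The case against.** The strongest reply is that the loss of power nearly vanishes under the analysis that will be run. Step 3 lowers the rate but still discards a fifth of the residents, whom section 6.1 keeps. Once both inputs follow section 6.1, the lower rate and the unneeded attrition allowance almost cancel. The shortfall below 80% at 30 per home is already present with the SAP's own 24%, so it comes mainly from the design effect. This stands, and it limits the point to a planning calculation that is wrongly built rather than a trial shown to be short of power.

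A reader might also halve the compounded any-admission figure, 1 − 0.88⁴ = 40.0%, to get 20.0% and a larger loss. The documents do not support that. The half is a share of hospitalizations, not of residents; applying it after compounding gives a resident with several admissions only one chance of going through the ED, which conflicts with the independence assumed. (The 19.7% in step 4 has a different source, namely deaths counted as No.)

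Two further replies hold in part. The survey counts admissions to hospital services, whereas the endpoint is admission to an ED. ED visits without a hospital stay may be missing from the survey figure and could raise the rate, by an amount the SAP does not give. And section 3.3 summarises a past calculation that no test or population uses. That makes the matter modest, but the section still stands as the justification of 1,000 per group.

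**Conclusion.** The scaling step is invalid for the endpoint. Under the plan's own 6% per quarter the rate is about 21.9%, or about 19.7% with deaths counted as No. Taken alone, the scaling error costs about 5 points of power or 12% in sample size. Taken with the attrition mismatch, the net effect is under 1 point at a given cluster size: about 77–79% power at 30 per home and 80–82% at 24.

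A reader might infer that the trial really has 75% power. The documents do not support this, because that figure still discards the deaths that section 6.1 keeps.

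One limit on the offset: if the SAP's design effect used 24 because deaths were removed, keeping them returns the cluster size to 30. The comparison is then 80.8–82.6% against 76.9–78.8%, about 4 points. The SAP does not settle this.

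Assumptions: equal and independent quarters (repeat admissions in the same frail residents would lower the rate further), constant hazards, a 30% relative reduction in the analysed proportion, and no ED visits beyond those in the survey figure. Confidence is moderate.

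**What to change.** In section 3.3, and where the front summary repeats it:

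- Replace 24% and 16.8% with rates for the binary endpoint: about 22%, or about 20% with deaths counted as No, each with its 30% reduction.
- Drop the attrition inflation for deaths that section 6.1 retains.
- State the cluster size used in the design effect.
- Restate the power, or the detectable reduction, for 1,000 per group.
- Record as assumptions that quarters are independent and that ED visits without admission could raise the rate.

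If section 3.3 must stay as a record of the protocol, put the restated figures in section 2, which already lists departures from it. The primary endpoint rule, the model and the populations stay unchanged, and no extra recruitment is asked for. The cost is a text change in the SAP.

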## 4 EVALUATION CRITERIA

### 4.1 Primary endpoint

The primary endpoint of this study, collected by subject, will be the occurrence of at least one admission to a hospital ED during a one-year follow-up period (i.e., yes / no binary criterion).

### 4.2 Secondary endpoints

To complete the main analysis of the impact of MDTM on transfers to ED, the following additional criteria will also be analyzed: the occurrence of at least one admission to a hospital emergency department during an 18-month follow-up period (i.e. binary yes / no criterion).

All of the following secondary endpoints are defined according to the secondary objectives to which they respond.

To determine the impact of systematic detection of dementia during MDTM on:

#### a- The quantity and type of non-drug treatments

The endpoint to meet this objective will be the changes of non-drug (paramedical) prescriptions such as physiotherapy, occupational therapy, psychomotricity, psychological counseling, dietetics, speech therapy or other care during the 18 months of follow-up since the inclusion (ie binary yes / no criterion). The changes will be analyzed first globally then separately for each type of care cited. The changes include stopping, increasing or decreasing the periodicity and the introduction of a care.

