### 6.3 Analysis of the secondary endpoints

#### 6.3.1 General

All secondary endpoints will be previously described by NH randomization group of subjects (intervention or control) and in total. The quantitative criteria will be summarized by their

|                    |                                                                   |                                                                                                            |
|--------------------|-------------------------------------------------------------------|------------------------------------------------------------------------------------------------------------|
| Principal analysis | Statistical Analysis Plan (SAP)-IDEM Study 0910701
Version 1.0 | [figure not shown]
Hôpitaux de Toulouse |
|                    |                                                                   | 07/22/2016                                                                                                 |

mean, standard deviation, median, 1st and 3rd quartile (Q1 and Q3), minimum and maximum. For the qualitative criteria, the number and percentage corresponding to each category will be presented.

All statistical tests performed to meet the secondary objectives will be bilateral with a risk of the first species at 5%. All these tests will have to be considered as purely exploratory not guaranteeing a global risk on the study of 5% (multiplicity of the tests).

The 18-month follow-up period for the secondary endpoints begins at the end of the inclusion wave in the center (i.e., the start date for the collection of judgment criteria).

Population of analysis: The analyzes on the secondary criteria of judgment will be made on the subjects of the ITT population for which the endpoint is available, except if another population is defined explicitly.

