### 6.3.3 The quantity and type of non-drug treatments

The modification of the prescription of a non-drug treatment will be modeled using a mixed logistic regression model with the randomization group as the fixed effect and the center as a random effect to estimate the impact of the group on the occurrence of the criterion.

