### 6.5.3 Description of data collected at inclusion

The characteristics found in the randomized NH centers (randomization stratification factors, number of residents included) will first be described.

The following characteristics of the subjects identified for inclusion in the study will be described for the entire analysis population and will be described in the 2 groups (intervention, control):

- Criteria for inclusion and non-inclusion;
- Sociodemographic characteristics (age, sex, marital status, education, mother tongue (French yes / no), occupation (yes / no), seniority in the NH (in months);
- Medical history and associated pathologies (visual or auditory impairment, smoking and alcohol consumption, total Charlson Comorbidity Index score);

|                    |                                                                   |                                                                                                            |
|--------------------|-------------------------------------------------------------------|------------------------------------------------------------------------------------------------------------|
| Principal analysis | Statistical Analysis Plan (SAP)-IDEM Study 0910701
Version 1.0 | [figure not shown]
Hôpitaux de Toulouse |
|                    |                                                                   | 07/22/2016                                                                                                 |

- Cognitive antecedents (progressive decline yes / no, MMSE test yes / no and score, cognitive assessments yes / no and type of assessment);
- Family history of dementia (presence of family history of dementia yes / no);
- Hospitalizations during the last 3 months by type of hospitalization (planned or in emergency) and by type of service;
- Ongoing drug and non-drug treatments at inclusion by type of treatment;
- Anticipated prescriptions by type;
- GIR total score at inclusion.

The following results from the Comprehensive Geriatric Assessment (CGA) obtained during the inclusion visit only for the intervention group, will be described:

- Overall MMSE score;
- Results of the clock test (score and normality);
- Results of the Borson Mini-Cog (normality);
- Overall score of the 5 word test;
- Categorical verbal fluency test results (total words generated, total acceptable words);
- Confusion Assessment Method (CAM) test result (acute confusional state yes / no);

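### The only endpoint for non-drug care pools starts and increases with stops and decreases, so the quantity part of that secondary objective goes unanswered

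*SAP*

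**What the plan says.** Section 3.2 of the SAP sets the objective, covering "the quantity and type of drug prescriptions" and, in the same bullet, "and non-drug treatments (physiotherapy, occupational therapy, psychological counseling, dietetics, speech therapy". Section 1 hands drug prescriptions to separate work, so the non-drug half is left to this SAP.

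Section 4.2 a gives one endpoint for it: changes in paramedical prescriptions "during the 18 months of follow-up since the inclusion (ie binary yes / no criterion". It then defines what counts as yes: "The changes include stopping, increasing or decreasing the periodicity and the introduction of a care". The planned breakdown is by kind of care: "The changes will be analyzed first globally then separately for each type of care cited".

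Section 6.3.3 carries this into the analysis: "The modification of the prescription of a non-drug treatment will be modeled using a mixed logistic regression model", with randomisation group as fixed effect and centre as random effect. Direction of change appears in neither section.

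**The concern.** An objective about the quantity of care needs an endpoint that can move up or down with quantity. This one codes a resident who loses physiotherapy and a resident who gains it identically. An odds ratio above 1 would fit more care, less care, or only more frequent re-prescribing. An odds ratio near 1 would fit no effect, or opposite shifts that cancel.

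This matters because sections 5 and 10 of the summary (the study diagram and the expected outcomes) present the team meeting as the place where a care plan, including non-pharmacological approaches, is discussed. A reader of the results will want to know whether it brought residents more of that care, and the planned analysis cannot say.

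**Working it through.** **Is direction recovered anywhere else in the SAP?** There is no planned figure to reproduce, because the SAP gives no rate, effect size or power for this endpoint. The check is therefore first a reading of the text.

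- Section 4.2 a and section 6.3.3: any change, globally and by type of care, without direction.
- Section 6.3.1: secondary endpoints are first described by number and percentage per category. For a yes/no criterion the categories are yes and no.
- Section 6.5.3: "Ongoing drug and non-drug treatments at inclusion by type of treatment" are described, at inclusion only.
- Section 6.5.4: follow-up of meeting recommendations, in the intervention group only.
- Sections 6.5.5 and 6.5.6: follow-up and end-of-study descriptions, which do not list non-drug treatments.
- By contrast, in section 4.2 the GIR endpoint (d) is a signed difference and the advance-directive endpoint (g) counts additions. Both keep direction.

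No planned output compares gains or losses of non-drug care between the arms.

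**Illustration 1: cancellation.** All rates here are assumptions. Odds ratios are crude, before the centre effect. Let U be the share with a start or increase and D the share with a stop or decrease. If each resident changes in one direction only, any change = U + D.

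- Intervention: 0.40 + 0.10 = 0.50.
- Control: 0.25 + 0.25 = 0.50.
- Odds ratio = (0.50/0.50)/(0.50/0.50) = 1.0, although U and D each differ by 15 points.

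**Illustration 2: same odds ratio, opposite meaning.** Take a control arm with U = 0.17 and D = 0.23, so any change is 0.40.

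- Intervention U = 0.40, D = 0.10: any change 0.50, odds ratio (0.50/0.50)/(0.40/0.60) = 1.5, net +30 per 100 residents against −6 in control.
- Intervention U = 0.10, D = 0.40: any change 0.50, odds ratio again 1.5, net −30 against −6.

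**Illustration 3: residents with changes in both directions.** Over 18 months and several kinds of care a resident may have both. Any change then lies between max(U, D) and U + D. For the rates in illustration 1 that is 0.40 to 0.50 in the intervention arm and 0.25 to 0.50 in the control arm.

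- Lowest odds ratio: (0.40/0.60)/(0.50/0.50) = 0.67.
- Highest odds ratio: (0.50/0.50)/(0.25/0.75) = 3.0.

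The same directional rates can thus give an odds ratio anywhere from 0.67 to 3.0, depending only on how changes overlap within residents.

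**What a directional endpoint could detect.** This borrows the primary endpoint's planning values from section 3.3: 1,000 residents per arm, 20% attrition, ICC 0.02, 30 residents per home. Applying them to this endpoint is an assumption.

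- Cluster size after attrition: 30 × 0.8 = 24.
- Design effect: 1 + (24 − 1) × 0.02 = 1.46.
- Effective n per arm: 1,000 × 0.8 / 1.46 = 548.
- With any change at 40% in both arms, the planned test rejects at its 5% level. A start-or-increase endpoint at 25% against 15% has about 99% power, and at 23% against 17% about 70% (two-sided 5%, two proportions).

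**The case against.** The strongest reply is that any change is a coherent process measure. A meeting that reviews a care plan may add, adjust or withdraw care, and whether prescriptions were modified is a fair sign that a review took place. The by-type analysis also shows which kinds of care were touched, which answers the type part of the objective. Both points stand, and the criticism is limited to quantity.

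It is also true that the endpoint is secondary. Section 6.3.1 says "All statistical tests performed to meet the secondary objectives will be bilateral with a risk of the first species at 5"% and declares these tests purely exploratory. That lowers the weight of the point. It deals with multiplicity, though, and does not make an undirected odds ratio interpretable.

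Two stronger readings should not be drawn:

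- A reader might infer that care naturally withdrawn from frail residents could pass for an intervention effect. Homes are randomised 1:1, so such withdrawal is expected at similar rates in both arms. It would dilute a difference, not create one.
- A reader might infer that, with seven kinds of care, nearly everyone will count as changed. At an assumed 15% to 20% per kind, 1 − 0.85^7 = 0.68 and 1 − 0.80^7 = 0.79. These figures need independence between kinds of care. One review may well alter several together, which lowers the global rate, and the SAP gives no rates. The by-type analyses would in any case be far from a ceiling.

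**Conclusion.** The point holds for the quantity part of the non-drug objective: followed exactly, the plan cannot say whether the intervention led to more care or less. It does not hold as a claim that the endpoint is uninformative, nor that a real effect will in fact be hidden. The numerical examples show what the definition permits. They rest on assumed rates, and exact cancellation in the first one also needs each resident to change in one direction only. The conclusion itself follows from the definition and needs none of these rates.

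The weight is moderate to low. One exploratory secondary endpoint is affected, and the confirmatory analysis of emergency department transfer is untouched. A change is still worthwhile because it is cheap and makes the result readable.

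**What to change.** In section 4.2 a and section 6.3.3, define two binary endpoints over the 18 months, globally and for each type of care:

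1. at least one introduction or increase;
2. at least one stop or decrease.

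Analyse each with the mixed logistic model already planned. A resident with changes in both directions counts in both. For the per-type stop-or-decrease endpoint, take account of whether the resident was receiving that care at inclusion, which is already collected (section 6.5.3). Adjustment or restriction would do, but the SAP should state which. Keep any change as a descriptive process measure.

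The cost is a revised SAP version before analysis starts, a recode, and twice as many exploratory tests if any change is no longer tested. The recode assumes that the kind of change is recorded per type of care. The endpoint definition implies this, but the case report form is not shown. Two indicators still do not measure quantity in full, since one extra session counts the same as several new therapies. They do give the direction, which the present endpoint lacks.
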